## Abstract

**Background:**

According to the World Health Organization (WHO), intrapartum care is considered a platform for providing respectful, personalized, and women-centered services to women. This study aims to investigate the intrapartum care model proposed by WHO.

**Methods:**

This convergent parallel mixed-methods study will be carried out in qualitative and quantitative phases. In the quantitative phase (a quasi-experimental study), 108 pregnant women admitted to the maternity ward will be randomized to intervention (receiving intrapartum care based on the WHO model) and control group (receiving routine hospital care) before the beginning of the active stage of labor (cervix dilatation equal to 5 cm) and Wijma's delivery fear scale (DFS) will be completed for them and again at 7–8 cm dilatation. The participants of both groups will be followed up for 6 weeks after labor and then they will be invited to a relatively quiet place to complete the Childbirth Experience Questionnaire (CEQ 2.0), the Edinburgh Postpartum Depression Scale (EPDS), the Post-Traumatic Stress Disorder (PTSD) Symptom Scale (PSS-I), the Pregnancy and Childbirth Questionnaire (PCQ), exclusive breastfeeding and a checklist on willingness to give birth to another child. The qualitative phase will employ content analysis to explain mothers' views about the effects of this model especially subjective components of this model on their labor process after 4–6 weeks. The two phase's results will be discussed in combination.

**Discussion:**

The implementation of such care models is expected to prevent mental disorders caused by negative experiences of childbirth, and also, prevent uncontrolled increases in cesarean sections.

**Clinical Trial Registration:**

https://fa.irct.ir/user/trial/68313/view, identifier (IRCT20120718010324N69).

## Introduction

Pregnancy and childbirth are among the most important experiences of women throughout their lives. The needs and problems of women during pregnancy, labor, and childbirth and the way they are addressed can substantially influence the whole meaning of the fertility process (1). Since mothers never forget their childbirth experiences, providing proper care for pregnant women can create a positive childbirth experience for them with a sense of control, independence, satisfaction, and confidence to mothers and also positively influence their desire to have children again in the future (2). The importance of positive childbirth experiences requires healthcare providers to not only strive to improve the physical health of mothers but also address their mental health (3). A negative childbirth experience can result in post-traumatic stress disorder (PTSD), disordered interpersonal relationships, inefficient mother-infant communication, low rates of exclusive breastfeeding, inappropriate use of maternal and infant care services, fear of future deliveries, and increased desire for elective cesarean section in future pregnancies (4, 5).

Technological advances in obstetrics and gynecology changed childbirth into a biomedical model over the past century (6). Accordingly, traditional labor at home was gradually supplanted by labor at hospitals and medical centers, and childbirth was turned into a medical procedure in most countries that is fully supervised and controlled by a physician (7). However, modern childbirth care has caused pregnant women to consider themselves patients and to lose the independence and control necessary for childbirth management. Midwives can play an important role in providing care that supports the physiologic nature of labor and childbirth, reducing unnecessary interventions and increasing the quality of care for mothers and newborns (8, 9). Therefore, the World Health Organization (WHO) recognized the requirement to introduce appropriate intrapartum care according to evidence-based medicine (10).

Accordingly, WHO in 2015 presented a global perspective in which every pregnant woman and her infant should receive high-quality antenatal, intrapartum, and postpartum care. This initiative also specified how healthcare staff had to provide such services in healthcare systems and how pregnant women and their families had to be treated when receiving such services. In addition, WHO has specified that effective communication, respect, dignity, and emotional support are the main components areas of healthcare quality that should be taken into account for improving the quality of services provided to pregnant women and infants (11).

This organization further emphasized the quality of such services through its 2018 recommendations on intrapartum care for a positive childbirth experience. Going beyond merely the prevention of pregnancy mortality, these recommendations involve a women's rights-based approach to optimizing the health and well-being of pregnant women and their infants (12, 13).

Analysis of the evidence supporting the WHO recommendations on intrapartum care shows that women expect a childbirth experience to meet or go beyond their previous personal and socio-cultural beliefs and expectations (13, 14). According to the recent WHO recommendations, women's experience of intrapartum care is considered an important aspect of high-quality care and not merely a complement to clinical procedures (13). The main principles of the 2018 WHO guidelines that include 56 evidence-based recommendations are as follows: (I) labor and delivery should be personalized and woman-centered, (II) no labor interventions should be done without specific medical indications, (III) only interventions with an immediate purpose that have been proven beneficial should be performed, and (IV) Only one clear goal, which includes the creation of a positive experience for pregnant women as well as their infants and family members, should take precedence over the intrapartum care. 2018 WHO guidelines also provide individual recommendations and how they affect the realization of a positive experience by women (12).

According to the WHO model, intrapartum care is considered a platform for providing respectful, personalized, woman-centered, and effective clinical and non-clinical services to pregnant women and an opportunity for skilled healthcare providers to optimize birth outcomes for women and their infants in a well-functioning system. To achieve these goals, WHO has proposed a woman- and infant-focused model of intrapartum care. The nine dimensions of this model are as follows: (1) respectful labor and childbirth care, (2) emotional support from a companion of choice, (3) effective communication by the staff, (4) pain relief strategies, (5) regular monitoring of labor, documentation, auditing, and feedback, (6) receiving oral fluids and food, (7) maternal mobility and birth position of choice, (8) a pre-established referral plan, and (9) continuity of care (12, 13). To implement this model more easily and effectively, the WHO developed and designed a next-generation partograph known as the “Labor Care Guide” (LCG) for healthcare providers to monitor the well-being of mothers and newborns during labor. This tool aims to ensure the provision of evidence-based high-quality care and stimulate shared decision-making by healthcare providers and women (15).

Studies in Iran show that there is no effective and acceptable communication between staff and pregnant women in the maternity wards (16, 17). Also, most Iranian mothers (75%) report one or more instances of non-respectful maternal care (18). Studies show that in settings with poor labor resources and a lack of multidisciplinary teamwork, implementing communication interventions during labor and childbirth may not be feasible in the long term (19, 20). According to the WHO, policy development that promotes the provision of high-quality care requires addressing multiple areas of maternity respectful care and effective staff communication with pregnant women during labor and childbirth. One of the most important measures in this direction is improving interactions at the level of the health system and providing multidisciplinary care. Also, holding regular multidisciplinary meetings to discuss and review communication approaches with women during labor and childbirth is one of the other recommendations of the WHO in this regard (13).

Maternal satisfaction with previous childbirth experiences can play a major role in a woman's decision about the type of childbirth (21). For example, dissatisfaction with the first childbirth experience may increase the desire for a cesarean section in future deliveries (18). The literature review did not yield any studies that dealt with all the components of the 2018 WHO intrapartum care model. Moreover, few qualitative studies were conducted on this subject, most of which were not comprehensive and discussed only some components of this model such as respectful maternal care and continuity of care (22–24). In line with the population policies of the Iranian government and the promotion of intrapartum care, this study on the 2018 WHO intrapartum care model is expected to lead to an increase in women's positive experiences of labor and their desire for giving birth to another child through normal vaginal delivery and also to reduce the rate of unnecessary cesarean sections.

### Study aim

Implementation and evaluation of the 2018 WHO intrapartum care model.

## Methods

### Study design

This convergent parallel mixed-methods study will be carried out in two phases: the quantitative phase (a quasi-experimental study) and the qualitative phase. The qualitative and quantitative data will be collected and analyzed simultaneously but independently. The data relating to the two phases will be analyzed separately but the results will be combined when interpreting the data (Figure 1).

**Figure 1 F1:**
[figure not shown]
Study visual diagram.

### Study phases

#### Quantitative phase

The quasi-experimental design was opted for instead of a randomized control trial because the intervention under study incorporates an accepted and well-established intervention and also, to sidestep the increased risk of contamination in the control group (25). The quantitative phase will be conducted on the pregnant women admitted to the maternity wards of Alzahra and Taleghani hospitals in Tabriz City.

#### Study settings

This study will be conducted in two public and also, specialized obstetrics and gynecology hospitals in Tabriz City, Iran (Alzahra and Taleghani). The necessary arrangements were made with the officials of the hospitals and the availability of the required equipment will be ensured before the beginning of the project. In case of any problem during the execution of the study, it will be reported. Alzahra Hospital is a Medical Education and Research Center and also, is one of the gynecological and obstetric referral centers in the northwestern region of the country. This center has 10 labor and delivery rooms (LDR). Taleghani Hospital is another Medical Education and Research Center in Tabriz and generally, mothers with low-risk conditions are admitted there. This center has eight LDRs. Each LDR in these centers is equipped with mother and neonate resuscitation facilities, fetal heart rate monitoring, a warmer, a suction device, a bathroom, and a birth ball. Also, pharmacological pain relief methods are performed at the request of mothers.

#### Specific objectives

1.To compare the childbirth experience between the intervention (receiving intrapartum care based on the WHO model) and control group (receiving routine hospital care)2.To compare the fear of childbirth between the study groups3.To compare the quality of intrapartum care between the study groups.

#### Secondary objectives

1.To compare the postpartum depression between the study groups2.To compare the PTSD six weeks after childbirth between the study groups3.To compare the desire to give birth to another child six weeks after childbirth between the study groups4.To compare the frequency of normal vaginal delivery between the study groups5.To compare the mean Apgar score for the infants between the study groups6.To compare the duration of the active stage of labor between the study groups7.To compare the duration of the second stage of labor between the study groups8.To compare the duration of the third stage of labor between the study groups9.To compare the exclusive breastfeeding 4–6 weeks after childbirth between the study groups10.To determine the face, content, and construct validity and also the reliability of the Pregnancy and Childbirth Questionnaire (PCQ).

### Inclusion and exclusion criteria

The inclusion criteria are the first or second delivery of women and before the beginning of the active phase of labor (cervix dilation equal to 5 cm). The exclusion criteria are multiple pregnancies, non-cephalic presentation, indications for a cesarean section (e.g., abnormal presentation, placenta previa, etc.), obstetric problems (such as placenta previa, vaginal birth after cesarean, placental abruption, and preeclampsia), maternal underlying conditions such as cardiovascular disease and diabetes), maternal mental disabilities and other mental health problems, and the death of a loved one over the last three months.

### Sample size

The sample size was calculated in G-Power based on the two primary outcomes of the childbirth experience and fear of childbirth. According to the findings of Shakarami et al. (26) regarding the fear of childbirth and assuming *M*_1 _= 69.3, *M*_2 _= 58.9 (considering a 15% clinically significant increase caused by the intervention based on expertise panel), SD_1 _= SD_2 _= 8.5, two-sided *α* = 0.05, and test power = 95%, the calculated sample size (*n*) was 19. Moreover, according to the findings of Ghanbari et al. (27) about childbirth experience and assuming *M*_1 _= 2.71, *M*_2 _= 3.25 (considering a 20% clinically significant increase caused by the intervention based on expertise panel), SD_1_ = SD_2_ = 0.73, two-sided *α* = 0.05, and test power = 95%, the sample size (*n*) increased to 49. Finally, assuming an attrition rate of 10%, the final sample size (*n*) in each group will be 54. This sample size has the power of 99% to test between-group differences in terms of fear of childbirth.

### Sampling

To collect the data, the researcher would refer to the maternity wards of Al-Zahra and Taleghani hospitals, and the participants will be selected from among those who meet the inclusion criteria through convenience sampling. After briefing the eligible women on the research objectives and procedure, written informed consent will be obtained from those who are willing to participate in the study. The participants will be randomized to the control or intervention groups at the beginning of the active phase of labor.

### Randomization and allocation concealment

The participants will be assigned to the study groups by stratified block randomization method (first or second childbirth of woman) in blocks of 4 and 6 and with a 1:1 allocation ratio. For allocation concealment, the intervention name will be written on pieces of paper and put in a series of numbered sealed opaque envelopes. The envelopes will be kept by the head of the maternity ward. After entering the qualified woman and obtaining the informed consent, her name and medical file number will be written on the envelope by the researcher and it will be opened by the head of the ward. After determining the type of intervention, the envelope will be returned to the head of the ward.

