### Blinding

It is noteworthy that the nature of this study does not allow for blinding the researcher and participants. To blind data collectors, the questionnaires for the postpartum stage will be completed by the researcher's assistant. Also, the data analyst will be blinded to group assignments.

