### Intervention

After assigning the participants to the study groups, socio-demographic and obstetrics characteristics questionnaires will be filled out for all of them. Then the researcher will implement the WHO intrapartum care model for those in the intervention group, whereas those in the control group will receive routine care by staff. The implementation of the study is in the form of multidisciplinary teamwork. The researcher who will implement the intrapartum care model is PhD student of midwifery (first author). She has attended workshops on making childbirth pleasant and physiologic childbirth and also worked for four years as a physiologic childbirth tutor in a health center. In the case where advice is needed or in unpredictable high-risk cases, the gynecologist involved in the study project will be contacted (second & fourth authors). The implementation of care will be monitored by the project supervisors who are reproductive health specialists (third and corresponding authors).

The intervention based on the 9 components of the WHO intrapartum care model is as follows:

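### The unblinded researcher who appears both to recruit by convenience sampling and to deliver the intervention could predict up to about 69% of next allocations, which opens a route to selection bias that sealed envelopes do not close

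*Protocol article*

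**What the plan says.** All references are to the Methods of the protocol article.

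- **Sampling.** The researcher goes to the maternity wards of both hospitals, and "the participants will be selected from among those who meet the inclusion criteria through convenience sampling". Consent comes first; randomisation follows at the start of active labour.
- **Randomization and allocation concealment.** Allocation is 1:1 by a "stratified block randomization method (first or second childbirth of woman) in blocks of 4 and 6". The slips are "put in a series of numbered sealed opaque envelopes". "The envelopes will be kept by the head of the maternity ward". After consent, the woman's name and file number are "written on the envelope by the researcher and it will be opened by the head of the ward".
- **Blinding.** The article states that "the nature of this study does not allow for blinding the researcher and participants". Only the postpartum data collector and the analyst are blinded.
- **Intervention.** "the researcher will implement the WHO intrapartum care model for those in the intervention group", while controls receive routine staff care. That researcher is one person and an author of the article that prints the block sizes.
- **Outcomes.** The three primary outcomes are childbirth experience, fear of childbirth and satisfaction with intrapartum care. All are reported by the women themselves.

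**The concern.** A sealed envelope stops the recruiter from reading the current slip. It does not stop her from inferring the slip from those already opened. In permuted blocks, the arm that is behind within a stratum is more likely to come next. Anyone who sees past allocations and knows that the blocks are short can use this.

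Here the person who treats every intervention woman necessarily learns the arms as the trial proceeds, and she also appears to be the person who recruits. Convenience sampling is the stated method, and it leaves open whom to approach and when.

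If the decision to approach a woman, or its timing, came to depend on the likely next arm, the groups could differ at entry in traits such as distress or cooperativeness. Those traits could influence self-reported experience and fear, and they are not among the socio-demographic and obstetric items listed under Data collection tools.

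**Working it through.** **Inputs from the article.** Block sizes 4 and 6, 1:1, two parity strata; 108 women, 54 per group. For childbirth experience (CEQ), the planned means are 2.71 and 3.25 (difference 0.54) with SD 0.73. The article gives no guessing probability, so there is no stated figure to reproduce on that point. The sample size that sets the scale does reproduce: a two-sample t-test with difference 0.54, SD 0.73, two-sided 5% and 95% power gives 49 per group, as stated.

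**Assumptions.** The guesser tracks each stratum separately, block sizes are equally likely in random order, and the strata hold 54 women each.

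**Step 1: guessing rate.** The rule is to guess the arm that is behind in the stratum, and to toss a coin when the arms are level. In a block of size 2b, the expected number of correct guesses is b + (2^(2b)/C(2b,b) − 1)/2.

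- Block of 4: 2 + (16/6 − 1)/2 = 2.833, so 2.833/4 = 70.8%.
- Block of 6: 3 + (64/20 − 1)/2 = 4.1, so 4.1/6 = 68.3%.
- Equal numbers of each: (2.833 + 4.1)/10 = 69.3%.

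The rule does not need the order of the blocks, because the imbalance returns to zero at each block end. Simulation with the order unknown gives 69.0%. It also gives 69.0% with strata of 70 and 38, and 68.3% if each hospital has its own list (four sequences of 27). Unpredictable allocation would give 50%.

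**Step 2: what the average hides.** In the same simulation about 6% of assignments are certain, about 48% can be guessed with probability 0.75 or more, and about 39% are a coin toss.

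**Step 3: pending women.** Consent precedes randomisation, so some allocations may still be unknown when the next woman is approached.

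| Same-stratum women consented, not yet randomised | Correct guesses | Guessable at 0.75 or more |
|---|---|---|
| 0 | 69% | 48% |
| 1 | 59% | 12% |
| 2 | 56% | 1% |

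**Step 4: illustrative effect on the test.** Score the guess +1 (intervention), 0 (level) or −1 (control). With accuracy a, the difference between arms in mean guess is 2(2a − 1). For a = 0.69 this is 2 × 0.38 = 0.76; for a = 0.59 it is 2 × 0.18 = 0.36.

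Suppose a guess shifts the enrolled woman's expected outcome by s SD in the guessed direction. Women enrolled under opposite guesses then differ by 2s. The CEQ bias is s × 0.76 × 0.73, and the noncentrality of the t-test with 54 per arm is s × 0.76 × √(54/2) = s × 3.95.

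| s (assumed) | Bias, none pending | True error, none pending | True error, one pending |
|---|---|---|---|
| 0.1 | 0.06 points | 6.8% | 5.4% |
| 0.2 | 0.11 points | 12.3% | 6.6% |
| 0.3 | 0.17 points | about 22% | 8.6% |

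Against the planned difference of 0.54, biases of 0.11 and 0.17 are about 20% and 31%. With 49 evaluable per arm and none pending, the error rates are 6.6%, 11.6% and about 20%.

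**Step 5: does a larger block help?** Adding blocks of 8 (random 4, 6 and 8) lowers the guessing rate only to 68%.

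**The case against.** Numbered sealed opaque envelopes, held and opened by the ward head after consent, with two block sizes, are a conventional procedure. Some predictability remains in any unblinded blocked trial. That is correct, and the procedure is not in itself an error.

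A reader might infer that the researcher hand-picks women, or that she will enrol according to her guess. The documents support neither. Convenience sampling ordinarily means taking accessible eligible admissions, and nothing says that enrolment will follow a prediction. That recruiter and provider are the same person is the natural reading of a repeated term, but it is not stated outright.

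A reader might also infer that the bias must favour the WHO model. No passage fixes a direction, and the SD shifts are assumptions without a source in the article. The error rates come from an unadjusted t-test, while the plan also has a covariate-adjusted model. Fear is measured before active labour, so an imbalance in distress could be seen, although Data analysis does not name baseline fear as a covariate.

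A workload motive is also tempting: one provider and two hospitals make a second simultaneous intervention woman hard to serve. But the article describes multidisciplinary teamwork and does not say how overlapping labours are handled.

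Finally, a condensed article may omit a screening log or the name of the person who generates the sequence, and those absences are not faults. What stands is the combination that the article itself states: convenience sampling, an unblinded researcher who delivers the intervention, and short blocks whose sizes she knows.

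**Conclusion.** The point holds as an avoidable opportunity for selection bias, not as a demonstrated bias. The guessing rate of about 69% is an upper bound. It requires that recruiter and provider are one person, that she tracks each stratum, and that no allocation is pending. With one or two pending women of the same stratum it is about 59% or 56%.

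The true error of about 7% to 22% is likewise a ceiling for assumed shifts of 0.1 to 0.3 SD in each direction. With one pending woman it is about 5% to 9%. If enrolment does not respond to the guess, there is no bias from this source. The sample-size calculation is unaffected. The change is worth making because it costs little, not because the trial would otherwise be invalid.

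**What to change.** 1. **Sampling.** Replace convenience sampling with consecutive approach of every eligible woman on the ward admission list during recruitment shifts scheduled in advance. Log each woman passed over, with a reason. Log any pause in recruitment before the next envelope is opened. This is the essential step, because it removes the discretion that a guess could act on.
2. **Randomization and allocation concealment.** Have a team member who does not recruit generate the sequence, with block sizes in random order that are not disclosed to the researcher. As the article already prints 4 and 6, this means a new list. Larger blocks alone are not a substitute, as the 68% shows.

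A ban on allocation while an intervention woman is in labour is not recommended. It would conflict with consecutive enrolment, and women who had already consented could reach active labour and be lost. Fixed shifts and logged pauses serve the same purpose.

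The cost is some extra logging, a new envelope list made by existing staff, and possibly slower recruitment.

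### Randomisation is stratified by parity but not by hospital, although two hospitals with differently described intake recruit; adding hospital as a stratum and model term is a cheap gain in balance and precision

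*Protocol article*

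**What the plan says.** Under Randomization and allocation concealment, the article specifies a "stratified block randomization method (first or second childbirth of woman) in blocks of 4 and 6", "with a 1:1 allocation ratio". The assignments are "put in a series of numbered sealed opaque envelopes", and "The envelopes will be kept by the head of the maternity ward". Parity is the only stratification factor given.

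Under Sampling, "the researcher would refer to the maternity wards of Al-Zahra and Taleghani hospitals", so there are two recruiting wards. Study settings describes Alzahra as "one of the gynecological and obstetric referral centers in the northwestern region of the country" and says of Taleghani that "generally, mothers with low-risk conditions are admitted there".

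The quantitative Data analysis section plans a general linear model that controls for socio-demographic and obstetric characteristics. It does not name hospital, and hospital is not among the items of the two baseline questionnaires under Data collection tools.

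**The concern.** The article chooses its stratification factor explicitly and leaves out the recruiting hospital. Hospital could plausibly relate to childbirth experience, mode of birth and length of labour, because intake is described differently and the control arm receives whatever routine care is given where the woman labours. Nothing stated keeps the arms alike in hospital mix, and no stated model term corrects for it afterwards.

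At stake are a little precision and how easily the result can be defended if the hospital mix turns out uneven. A smaller, practical gap is that one ward head is mentioned as envelope keeper while there are two wards. Custody matters here because the researcher who recruits also delivers the intervention and is unblinded.

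**Working it through.** **Inputs from the article.** Total 108 women, 54 per arm; 1:1 allocation; blocks of 4 and 6; parity strata. Childbirth experience, which drives the sample size: means 2.71 and 3.25, SD 0.73, two-sided α 0.05, power 95%.

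**Inputs assumed.** The hospital split is not given, so 50:50 and 70:30 are used. The parity split is not given, so 50:50 is used, with parity and hospital independent.

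**The plan's own figure.** The difference is 3.25 − 2.71 = 0.54. A two-sample t-test (noncentral t) needs 49 per group, with power 0.952. Then 49 × 1.1 = 53.9, rounded to 54, so 108 in total. The stated size is reproduced, and nothing below alters it.

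**Chance imbalance by hospital.** The stated scheme was simulated 6,000 times per scenario with random permuted blocks of 4 and 6. D is the absolute difference between the arms in the share of women from one hospital, in percentage points.

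| Strata | Hospital split | Mean D | 95th percentile | P(D ≥ 10) | P(D ≥ 15) | P(D ≥ 20) |
|---|---|---|---|---|---|---|
| Parity only | 50:50 | 7.7 | 18.5 | 0.29 | 0.10 | 0.04 |
| Parity only | 70:30 | 7.1 | 17.4 | 0.27 | 0.09 | 0.02 |
| Parity × hospital | 50:50 | 1.4 | 3.7 | 0 of 6,000 | 0 | 0 |
| Parity × hospital | 70:30 | 1.6 | 3.7 | 0 of 6,000 | 0 | 0 |

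**Check by hand.** Without balancing on hospital, the SD of the difference in share is about √(4p(1−p)/108).
- p = 0.5: √(1/108) = 0.096. P(|Z| ≥ 0.10/0.096) is about 0.30.
- p = 0.7: √(0.84/108) = 0.088. P(|Z| ≥ 0.10/0.088) is about 0.26.

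Both agree with the simulation. An exact hypergeometric calculation, which fixes the hospital totals and treats allocation as a simple draw of 54 from 108, gives 0.336 (54 women at one hospital) and 0.292 (32 women). The simulated figures are preferred because they follow the stated block scheme.

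**What an imbalance does to the estimate.** Shift in the unadjusted contrast = imbalance × hospital effect. The hospital effect is unknown; take 0.5 SD as an assumption.
- 10 points: 0.10 × 0.5 = 0.05 SD.
- 15 points: 0.15 × 0.5 = 0.075 SD.
- Planned difference: 0.54/0.73 = 0.74 SD.
- Ratios: 0.05/0.74 = 7% and 0.075/0.74 = 10%.

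With a hospital effect of 0.25 SD these halve, to about 3% and 5%.

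**Precision.** Hospital would account for about p(1−p) × effect² of the outcome variance. At a 50:50 split this is 0.25 × 0.5² = 6% for an effect of 0.5 SD, and 0.25 × 0.25² = 1.6% for 0.25 SD. That is what leaving hospital out of the model gives up.

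**The case against.** Stratifying by site is common practice, but omitting it is neither an error nor a contradiction. Randomisation keeps the comparison unbiased whatever the realised hospital mix. Nor is hospital shown to be prognostic. Both are public teaching hospitals in one city with similarly equipped delivery rooms, and routine care is described once for both. The contrast in intake concerns general admissions, while the trial excludes at both sites women with, among other things, "obstetric problems (such as placenta previa, vaginal birth after cesarean, placental abruption, and preeclampsia". The exact covariates may also be listed in an analysis plan that is not shown. All of this stands, and it makes the point an improvement and not a defect of validity.

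A reader might go further and infer that there is one envelope series with one keeper, so that it cannot be opened in number order at two sites and concealment fails. The article does not support that. It uses the singular for the maternity ward elsewhere even though there are two. Parity strata already need at least two sequences, so the wording cannot be a literal count. A single researcher moving between wards could also draw a shared series in order. The article states real safeguards: consent first, identifiers written on a sealed opaque envelope before it is opened, and opening by the ward head.

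The two issues also hang on one unstated fact. If each ward already holds its own parity-specific envelopes in complete blocks, allocation is in effect stratified by hospital and most of the imbalance disappears.

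The remaining point is that the text names parity as the only factor, leaves the arrangement across two wards open, and does not name hospital in the model.

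**Conclusion.** The point holds as a worthwhile, low-cost improvement. As written, parity-only blocking leaves roughly a 27% to 29% chance of a between-arm difference of at least 10 points in hospital share, which stratifying by hospital would all but remove. The figures rest on assumed hospital and parity splits and on envelopes not already being blocked within hospital.

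It should not be read as bias in the randomised comparison. The consequence is some lost precision and a possible shift in the realised estimate. That shift is about 7% to 10% of the planned difference for imbalances of 10 to 15 points if the hospital effect is 0.5 SD, and proportionately less for a smaller effect. Neither the hospital effect nor the case-mix difference among eligible women is given. On the envelopes, the supportable statement is only that their division between the two wards is not described.

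**What to change.** Stratify by hospital and parity (four strata), keeping blocks of 4 and 6. Prepare a separate numbered envelope series for each stratum, held at that hospital's own maternity ward, and say so in the randomisation section. Include hospital and parity as fixed factors in the general linear model. If recruitment has started, keep the existing list, add hospital to the model and describe how the envelopes were actually divided.

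The cost is new lists, a sentence or two of text and one more model term. Hospital is known for every woman, so no extra data or participants are needed and 54 per arm stands. The downside is a few more incomplete blocks. Each stratum can end at most 3 women out of balance (half a block of 6), so the extreme overall difference between arm sizes rises from 2 × 3 = 6 to 4 × 3 = 12 of 108. Reaching that would need every stratum to stop at its worst point in the same direction.
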